## Abstract

Sarcopenia (SP) is an age-related disorder characterized by progressive loss of muscle strength, mass, and limb dysfunction, severely compromising the quality of life and life safety in older adults. With the global aging population, the incidence of this disease has been escalating, posing a significant public health challenge. Preclinical studies have demonstrated that acupuncture effectively mitigates muscle loss in rats; however, the field currently lacks robust randomized controlled trials (RCTs), marked by limitations such as the absence of sham acupuncture controls, multicenter designs, and standardized outcome metrics. Therefore, this study integrates acupuncture with exercise therapy, incorporating the following design highlights:

A multicenter approach to enhance research reliability;

A control group receiving sham acupuncture combined with exercise to eliminate the placebo effect;

The most comprehensive and validated set of outcome measures to ensure study rigor and expand the conceptual framework for sarcopenia assessment.

This research aims to provide robust evidence for acupuncture as an effective adjuvant therapy for SP. The study has been registered with the International Traditional Medicine Clinical Trials Registry Platform (ITMCTR2024000374).

AbbreviationsSPSarcopeniaRCTsRandomized Controlled TrialsASMAppendicular Skeletal Muscle MassSMISkeletal Muscle IndexDXAdual-energy X-ray absorptiometryQCTQuantitative Computed TomographyFTSSTFive-Times-Sit-to-Stand TestSPPBShort Physical Performance BatteryIGF-1Insulin-like Growth Factor-1TNF-αTumor Necrosis Factor-αIL-6Interleukin-6SODSuperoxide DismutaseGSH-PxGlutathione PeroxidaseCRCClinical Study CoordinatorECGElectrocardiogramFASFull Analysis SetPPSPer Protocol SetSSSafety SetITTIntention-To-TreatDMCData Monitoring CommitteeIECEthics Committee

**Specifications table**

**Table utbl0001:** 

**Subject area**	Medicine and Dentistry
**More specific subject area**	Traditional Chinese Medicine (TCM) and acupuncture for the treatment of musculoskeletal disorders.
**Name of your protocol**	Acupuncture combined with Exercise Therapy for Sarcopenia in the Elderly: A Multicenter Randomized Controlled Study Protocol.
**Reagents/tools**	Not applicable.
**Experimental design**	This study is a prospective, multi-center, parallel-group randomized controlled trial, which is a superiority intervention study. SP patients who meet the diagnosis and inclusion criteria will be recruited. Patients will be randomly assigned to two groups in a 1:1 ratio: the acupuncture group (receiving acupuncture at selected points combined with exercise therapy) and the sham acupuncture group (receiving sham acupuncture combined with exercise therapy). Both groups will be treated for 60 days and followed up for 90 days. Various efficacy indicators and safety indicators of the patients will be recorded before treatment, at 30 days of treatment, at 60 days of treatment, 60 days after the end of treatment, and 90 days after the end of treatment. After randomization, the Clinical Study Coordinator(CRC) will schedule treatment sessions. All recruitment procedures would be documented in the log file.This trial protocol uses the Standard Protocol Items :Recommendations for Interventional Trials (SPIRIT) reporting guidance Fig. 1 shows a flow chart of the study design.
**Trial registration**	The study has been registered with the International Traditional Medicine Clinical Trials Registry Platform (ITMCTR2024000374).
**Ethics**	The study protocol has been reviewed and obtained ethics approval from the IEC of The Affiliated Hospital of Shaanxi University of Chinese Medicine (SZFYIEC-PJ-2024No.[156]). All subjects involved in this study will sign the informed consent form. And our informed consent form contains the subjects' permission for all the data that we will collect and use. Further analysis of biological samples is not applicable to this study.
**Value of the Protocol**	1. SP severely compromises quality of life and survival in older adults, with its incidence escalating alongside global aging. However, mainstream treatments for SP are associated with limitations: exercise therapy alone suffers from low adherence, nutritional support carries the risk of exacerbating renal burden, and hormone therapy exhibits significant side effects. Thus, there is an urgent need to explore effective adjunctive and alternative therapies for SP. 2. Previous clinical studies on acupuncture for SP have been plagued by flaws such as the absence of multicenter designs and lack of sham controls. Therefore, this study will employ a multicenter RCT to enhance reliability, complemented by a sham acupuncture control group to minimize the placebo effect. 3. Previous research in this field has suffered from inconsistent and incomplete efficacy endpoints. Thus, this study introduces a comprehensive set of primary and secondary endpoints, encompassing muscle strength, muscle mass, physical function, and muscle-related serum biomarkers.

## Background

Sarcopenia(SP) is mainly characterized by the progressive loss of skeletal muscle mass and function [[1], [2], [3]]. As a disease closely associated with aging, the prevalence of SP has been increasing year by year along with the intensifying global aging trend, thus emerging as a global public health concern and a cutting-edge research topic. Worldwide, in the population of community - dwelling elderly individuals, the prevalence of SP spans from 10 % to 40 % [4]. The decreased muscle strength, reduced muscle mass, and limb dysfunction manifested by SP severely impair the quality of life and life safety of the elderly. Patients with SP have a 2 - 3 times higher risk of falling compared to the normal population [[5], [6], [7]]. The pathogenesis of SP involves multiple factors. Various chronic diseases, malnutrition, and lack of exercise that occur during the aging process of the human body [8,9], as well as inflammatory responses, oxidative stress, mitochondrial dysfunction, and neuromuscular junction degeneration at the molecular level, are all important contributors to SP [[10], [11], [12]].

Acupuncture represents an effective approach for the treatment of SP [13]. Acupuncture, based on the theory of Chinese medicine meridians, stimulates specific acupoints to regulate the circulation of qi and blood, the functions of zang-fu organs, and the waxing and waning of qi and blood in the meridians, thereby achieving the goals of strengthening the healthy qi, expelling pathogenic factors, and balancing yin and yang [5]. From the perspective of modern medicine, the mechanisms underlying acupuncture treatment for SP are multifaceted. It may regulate the neuroendocrine system, promoting the secretion of hormones related to muscle growth and repair, such as growth hormone and insulin-like growth factor-1 (IGF-1) [14]. This, in turn, stimulates muscle protein synthesis, inhibits muscle protein breakdown, and ultimately increases muscle mass and strength. Meanwhile, the anti-inflammatory and antioxidant effects of acupuncture contribute to alleviating inflammatory responses and oxidative stress damage in muscle tissues, protecting muscle fibers, improving the muscle microenvironment, and facilitating muscle repair and regeneration [5,10]. Additionally, acupuncture can modulate the function of the nervous system, enhancing neuromuscular conduction, increasing muscle excitability and coordination, and further elevating muscle strength and motor function. Some basic research and clinical observations have provided evidence to support acupuncture treatment for SP [5,14]. For instance, animal experiments have revealed that acupuncture intervention can significantly improve muscle mass, strength, and exercise capacity in animal models of SP [10]. The underlying mechanisms are associated with regulating muscle-related gene expression, promoting protein synthesis, and suppressing inflammatory responses. In clinical practice, several studies have also reported that acupuncture exhibits certain efficacy in improving SP that occurs concurrently with chronic diseases (such as chronic liver disease, chronic kidney disease, heart failure, etc.), manifested as enhanced muscle strength, improved limb function, and elevated quality of life [15,16].

However, there are relatively few RCTs in this area. Almost none of the existing RCTs have involved sham controls or multi-center studies to enhance reliability. The lack of unified observation indicators also poses challenges to sensitivity, specificity, and reproducibility [[17], [18], [19], [20], [21], [22], [23], [24], [25]]. Given the high prevalence and severe consequences of SP, as well as the potential multi-target action mechanisms and promising clinical application prospects of acupuncture in treating this disease, this protocol has been meticulously designed to observe the efficacy and safety of acupuncture combined with exercise therapy for SP, aiming to provide more scientific and reliable evidence for acupuncture as a reliable complementary therapy for SP.

## Description of protocol

1. Objectives:

This study is a multi-center, randomized, controlled clinical trial, aiming to observe the efficacy and safety of acupuncture combined with exercise therapy for SP, and to provide reliable evidence for acupuncture as a trustworthy complementary therapy in this field.2. Methods:

### Trial design

This study is a prospective, multi-center, parallel-group randomized controlled trial, which is a superiority intervention study. SP patients who meet the diagnosis and inclusion criteria will be recruited. Patients will be randomly assigned to two groups in a 1:1 ratio: the acupuncture group (receiving acupuncture at selected points combined with exercise therapy) and the sham acupuncture group (receiving sham acupuncture combined with exercise therapy). Both groups will be treated for 60 days and followed up for 90 days. Various efficacy indicators and safety indicators of the patients will be recorded before treatment, at 30 days of treatment, at 60 days of treatment, 60 days after the end of treatment, and 90 days after the end of treatment. After randomization, the Clinical Study Coordinator(CRC) will schedule treatment sessions. All recruitment procedures would be documented in the log file.This trial protocol uses the Standard Protocol Items :Recommendations for Interventional Trials (SPIRIT) reporting guidance [26]. Fig. 1 shows a flow chart of the study design.

**Fig. 1 fig0001:**
[figure not shown]
Flow chart of the study design.

### Study setting

The study sites include three tertiary hospitals in Shaanxi, China: (1) The Affiliated Hospital of Shaanxi University of Chinese Medicine, (2) Xi'an Honghui Hospital, and (3) Xi'an Hospital of Traditional Chinese Medicine. The reason why these three hospitals are selected to conduct the clinical trial is that they are equipped with comprehensive examination and treatment facilities. Enrolled patients will fill out questionnaires, undergo examinations, and receive treatment in these three hospitals. Considering that elderly patients with SP may have mobility problems, we plan to provide pick-up and drop-off services for the subjects, subject to the approval of the ethics committee. This is intended to show our concern for the patients and reduce the dropout rate.

### Eligibility criteria

#### Diagnostic criteria

In this study, the diagnostic criteria were formulated with reference to Sarcopenia in Asia: consensus report of the Asian Working Group for sarcopenia, 2019 [1](1)Preliminary screening: SARC—CalF questionnaire: a SARC—CalF questionnaire≧11 is classified as a positive SP screen;(2)Muscle power: Handgrip strength <28 kg for men and <18 kg for women;(3)Muscle function: Utilizing 6-meter walking speed and FTSST, 6-meter walking speed <1.0 m/s and FTSST >12 s. *Or sppb*≦9 points;(4)Muscle mass: DXA: ASM, Males <7.0 kg/m^2^, females <5.4 kg/m^2^.

The above item (1) is the case finding session, and (1)(2)(4) are performed on the patient when the SARC—CalF questionnaire is screened positive.

Diagnosis of SP: Decreased skeletal muscle content (positive for item (4))+decreased muscle strength (positive for item (2)) or decreased trunk function (positive for item (3));

#### Inclusion criteria

(1) Patients who meet the aforementioned diagnostic criteria. (2) Patients aged between 60 and 80 years old, regardless of gender. (3) Those who have agreed to participate in this study and have signed the informed consent form.

#### Exclusion criteria

(1) Individuals with severe primary diseases of vital body organs (such as the heart, kidney, liver, etc.) or important systems; (2) Those with limb diseases that prevent movement (e.g., fractures, cerebral infarction, cerebral hemorrhage, etc.) or a combination of diseases that affect body weight (e.g., long-term hormone users); (3) People with a certain degree of limitation in their ability to perform activities of daily living; (4) Persons with electronic devices or metal objects implanted in their bodies (e.g., pacemakers or artificial joints); (5) Individuals with severe psychiatric mental illness or cognitive dysfunction; (6) Those with underlying diseases (hypertension, diabetes, coronary heart disease, etc.) and whose underlying diseases are not in a stable stage; (7) Exclude patients with reduced muscle mass or muscle strength due to other causes (myasthenia gravis, spinal cord injury, diabetes, COPD, etc.); (8) Long-term bedridden patients due to post-stroke, spinal cord injury, physical disability, etc. are excluded; (9) Patients with other muscle diseases such as amyotrophic lateral sclerosis, myotonic dystrophy, etc. that lead to decreased muscle mass or muscle strength are excluded.

Fig. 2 shows the enrollment process.

**Fig. 2 fig0002:**
[figure not shown]
Flowchart of enrollment.

### Sample size

Regarding the design of the sample size calculation formula, we referred to the 8th edition of "Epidemiology" published by the People's Health Publishing House [27]. The formula is presented as follows: *N* = 2(Z₁₋α/₂ + Zβ)²σ²/d². In this formula, Z₁₋α/₂ represents the value corresponding to the first type of error probability, and Zβ denotes the value for the second type of error probability. σ is the standard deviation estimated through literature study [[17], [18], [19], [20], [21], [22], [23], [24], [25]], with σ=0.80 kg/m². d is the difference between the means of the two groups as estimated through literature study [[17], [18], [19], [20], [21], [22], [23], [24], [25]]. The mean value was 6.76 kg/m² in the acupuncture group and 6.08 kg/m² in the sham acupuncture group, thus *d* = 0.68 kg/m². Substituting the above data into the formula yields a sample size of 36 cases per group. Considering a 10 % dropout rate, the number of cases to be included in each group should be no <40. Since a 1:1 ratio is employed for both groups, 80 cases are needed at each center, totaling 240 cases.

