### Statistical methods

#### Statistical methods for primary and secondary outcomes

The main efficacy indicators will be analyzed using both the full analysis set (FAS) and per protocol set (PPS). The other efficacy indicators will be analyzed via the FAS set, while the safety indicators will be analyzed with the safety set (SS). The baseline equilibrium analysis will also be carried out using the FAS set.

Statistical analysis encompasses statistical description and statistical inference. For the statistical description of quantitative indicators, it includes mean, standard deviation, median, minimum value, and maximum value. Qualitative indicators are depicted by frequency tables and constituent ratios. Statistical inference involves interval estimation and hypothesis testing. For quantitative indicators, their two-sided 95 % confidence intervals (CIs) will be estimated. Each efficacy indicator will undergo bilateral testing with a significance level of α = 5 %. The null hypothesis posits that there is no statistically significant difference between the test group and the control group, whereas the alternative hypothesis contends that there is a statistically significant difference between the two groups. When *p* < 0.05, the null hypothesis will be rejected, and the difference between the two groups is deemed statistically significant.

Regarding measurement data, normality analysis is performed first. All data conforming to normal distribution are expressed as mean ± standard deviation. For comparison within the same group before and after treatment, the paired *t*-test is utilized, and for comparison between groups, the independent samples *t*-test is employed. For non-normally distributed measurement data, the rank sum test is adopted. For non-graded data in count data, the chi-square or non-parametric test is used. For graded data, the Ridit test is applied. In a bilateral test, a P value <0.05 is considered as a statistically significant difference.

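### The printed formula requires 80 patients in the whole trial, not 80 at each centre, and the literature mean labelled as sham needs its comparator clarified

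*Protocol article*

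**What the plan says.** The Sample size section of the protocol article uses the standard formula for comparing two means, 2(Z₁₋α/₂ + Zβ)²σ²/d². It explains the Z terms only in general: "Z₁₋α/₂ represents the value corresponding to the first type of error probability, and Zβ denotes the value for the second type of error probability". No value of β, and so no power, is given. The standard deviation is taken from references 17 to 25 ("with σ=0.80 kg/m²"). The difference d = 0.68 comes from the same references, as a mean of 6.76 in the acupuncture group less "6.08 kg/m² in the sham acupuncture group". The result is 36 per group, or at least 40 per group with 10% dropout. The section ends: "Since a 1:1 ratio is employed for both groups, 80 cases are needed at each center, totaling 240 cases".

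Three other places bear on this:

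- Sequence generation describes one central, completely randomised list of 240, split into 120 and 120. No stratification by centre is described.
- Statistical methods for primary and secondary outcomes sets the error rate ("Each efficacy indicator will undergo bilateral testing with a significance level of α = 5"%), names the independent-samples t-test for comparisons between groups, and plans two-sided 95% confidence intervals.
- Background says of the earlier literature: "Almost none of the existing RCTs have involved sham controls or multi-center studies to enhance reliability".

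**The concern.** The formula returns the number per group for one comparison of two groups. Doubling it gives the whole trial. The article presents that whole-trial figure as the need at each of three centres, and the only reason it offers is the allocation ratio, which has already been used in going from 40 to 80. A reader checking the calculation would find a stated need three times what the formula supports, and would take 0.68 kg/m² as the difference that 240 patients were chosen to detect. It is not: a trial of 240 is sensitive to much smaller differences.

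The second problem is the planning difference itself. It is presented as acupuncture against sham, but the article's own account of the literature leaves little sham-controlled evidence from which such a mean could come. If the 6.08 came from a comparator without sham needling, 0.68 mixes specific and non-specific effects and is not the contrast that this trial estimates.

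**Working it through.** **Inputs.** SD 0.80 kg/m² and d = 6.76 − 6.08 = 0.68 kg/m² (Sample size); two-sided 5% (Statistical methods); 10% dropout and 1:1 allocation (Sample size). Power is not stated and has to be inferred.

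**Reproducing 36 per group.** n per group = 2(z₀.₉₇₅ + z_power)² × 0.64 / 0.4624.

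| Power | Two-sided result | Rounded up |
|---|---|---|
| 80% | 21.73 | 22 |
| 85% | 24.85 | 25 |
| 90% | 29.09 | 30 |
| 95% | 2(1.960 + 1.645)² × 0.64 / 0.4624 = 35.97 | 36 |

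One-sided versions at the same four powers give 18, 20, 24 and 30. Of the values tried, only two-sided 5% with 95% power gives 36.

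**From 36 to the total.** 36 / 0.9 = 40 per group. 2 × 40 = 80 for the two-arm trial. 240 = 3 × 80, where 3 is the number of centres and appears nowhere in the formula.

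**Does the design supply the factor of three?** A requirement of 80 per centre would follow if each centre were to give its own adequately powered test. The article describes no such test. The single unstratified list would also not guarantee 40 per arm within a centre.

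**What 240 gives.** 120 × 0.9 = 108 evaluable per arm. The standard error of the difference is 0.80 × √(2/108) = 0.1089.

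- Power for 0.68: 0.68 / 0.1089 = 6.25; 6.25 − 1.96 = 4.29; power is above 99.99%.
- Detectable difference, (1.960 + z_power) × 0.1089: 2.802 × 0.1089 = 0.305 at 80%; 3.242 × 0.1089 = 0.353 at 90%; 3.605 × 0.1089 = 0.392 at 95%. That is about 0.31, 0.35 and 0.39 kg/m².
- The SD comes from the same literature as d, so a range is needed. If it lies between 0.6 and 1.0 (assumed), the 90% figure runs from 3.242 × 0.6 × 0.1361 = 0.26 to 3.242 × 1.0 × 0.1361 = 0.44 kg/m².

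**If the effect against sham is smaller than 0.68.** The article gives no separate sham-controlled effect. Over an assumed range, power with 108 per arm at SD 0.80 is:

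| True difference (kg/m²) | Power |
|---|---|
| 0.20 | 45% |
| 0.30 | 79% |
| 0.34 (half of 0.68) | 88% |
| 0.40 | 96% |
| 0.50 | 99.6% |

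**The comparator label.** Sample size assigns the 6.08 to a sham group found in references 17 to 25. Background says that sham controls are nearly absent from the existing trials. The two are not strictly incompatible, since one sham-controlled source could exist, but they do not fit together without an explanation.

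**The case against.** The best defence is that a larger trial does no harm to validity or power. On the stated inputs the trial has ample power for 0.68, and the planned confidence intervals will show what a null result excludes whatever difference was used for planning. That stands: a reader might infer that a negative result could not be interpreted, and the Statistical methods section does not support that.

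It can also be said that the article condenses a fuller protocol, and that 80 per centre may be a recruitment target or reflect an intended centre-level analysis. A recruitment target needs no stratified list, so this cannot be excluded. But the text says that 80 are needed at each centre and derives this from the allocation ratio, and that derivation is wrong whatever the intention.

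On the sham label, a reader might infer that 0.68 certainly comes from trials without sham. The documents do not establish this. In Background the marker for references 17 to 25 follows the next sentence, on the lack of unified indicators. Table 1 cites the same references for irisin and myostatin. Methods for additional analyses says that an unpublished meta-analysis helped with the sample size. The source trials are not at hand. What remains is a tension to be explained.

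A reader might go further and argue that 6.76 is out of reach, because patients enter below sex-specific limits ("Males <7.0 kg/m^2^, females <5.4 kg/m^2"). That needs a sex ratio which the article does not give, and it treats literature means as predictions for this trial when the formula uses only their difference. The lack of a calculation for handgrip, the other primary indicator, is likewise no error here, since a condensed article may leave it to the full protocol.

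**Conclusion.** The point holds in a limited form. On its own inputs the formula requires 80 randomised patients in total, and the stated need of 80 per centre is three times that, with no basis in the formula, the randomisation or the test described. The 36 and the 40 are correct if the intended power was 95%, which is inferred. At 240 the trial has 90% power for about 0.35 kg/m², not merely for 0.68, assuming SD 0.80 and 10% dropout. Separately, the sham label on 6.08 sits badly with the Background, so 0.68 may not be the expected difference against sham; whether it is cannot be settled from the article. This should be corrected, but it is a fault in the justification. It does not make the trial too small for 0.68, and it does not bias the comparison.

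**What to change.** Keep 240 and rewrite the end of the Sample size section:

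1. Delete the requirement of 80 at each centre. State that the formula, at its stated power (95% if that was intended), requires 36 per group, 40 after dropout and 80 in total. If a powered analysis within each centre is in fact intended, say so and describe it.
2. State what 240 provides: 120 per arm, about 108 evaluable after 10% dropout; over 99.99% power for 0.68 kg/m²; and 80%, 90% and 95% power for about 0.31, 0.35 and 0.39 kg/m² at SD 0.80. Add that the 90% figure is about 0.26 to 0.44 kg/m² if the SD is 0.6 to 1.0, marked as an assumed range.
3. Say which comparator gave the 6.08 mean. If it was not sham, state that 0.68 is not the expected effect against sham.

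This changes wording only; enrolment and design stay as they are. The cost is a less favourable rationale, since 240 is no longer presented as a derived need and the planning difference may lose its standing as a sham-controlled estimate. The article reports that recruitment is under way and outcome assessment has not been reached, so the restatement can still be made before results are known.
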